1. GENERAL INFORMATION

**Study title**: Elucidating the influence of lactulose intake on the gut microbiota composition.

1. STUDY SYNOPSIS

| Study Title: | Elucidating the influence of lactulose intake on the gut microbiota composition. |
| --- | --- |
| Protocol Version and Date: | Protocol ID: KEK-ZH-Nr.  Version: 1.0  Date: 16.6.2014 |
| Methodology: | This is a clinical study for investigating the influence of lactulose (as used for the lactulose breath test) on the composition and metabolic activities of the intestinal microbiota. Healthy volunteers will donate fecal samples and urine before (24 h) and after (1-2d, 14d) a routine lactulose breath test. Samples will be analyzed for their microbiota composition and key metabolites. |
| Study Duration: | Data acquisition for the study will be performed from October 2014 to March 2016. Total study duration for each participant is 4 hours maximum (including preparation time) at the study center for the breath test plus collection of fecal samples and urine. |
| Study Center: | Division of Gastroenterology and Hepatology  University of Zurich  [name]  [name] |
| Objective(s): | Primary objective:   - Influence of lactulose intake on gut microbiota composition   Secondary objectives:   - Influence of lactulose intake on metabolic profiles within the fecal ecosystem and the host (urine) |
| Number of Subjects: | 40 healthy volunteers |
| Diagnosis and Main Inclusion Criteria: | - Subjects free of abdominal complaints (=healthy). - Written informed consent - Working at ETH Zurich/University of Zurich, experience in handling of liquid nitrogen on biosafety level 2 |
| Main Exclusion Criteria: | - Age under 18 - Previous history of gastrointestinal disease or surgery (excludes appendectomy, hernia repair and anorectal disorders) - Known diabetes mellitus, scleroderma, neurological impairment or other major current disease - Subjects unable to stop medication that alters gut flora: proton pump inhibitors, laxatives and antibiotics at least 4 weeks before study entry. - Pregnancy beyond week 12 (no pregnancy test will be performed) - Involvement in any other clinical trial during the course of this trial, nor within a period of 14 days prior to its beginning or 14 days after its completion |
| Study Schedule: | October 2014 – March 2016: Recruitment, data collection and analysis. |
| Statistical Methodology: | Acquired H_2_-measurements and metabolic profiles will be analyzed according to standard algorithms. Several algorithms are available (see below). Microbial gut communities will be analyzed by 16S rRNA sequencing and compared using hpc-clust (see below). |
| Statement: | This study will be conducted in compliance with the protocol, the current version of the Declaration of Helsinki („59th WMA General Assembly“, Seoul, October 2008), and ICH-GCP as well as all national legal and regulatory requirements. |

- 1. Study Flow chart

Informed consent will be obtained during a separate visit. The study will be finished within 15 days for each individual, with one main study day. The following basic steps will be performed:

- Informed consent will be obtained during the first study visit. At that time,basic medical history and gastrointestinal complaints will be addressed, dates for the lactulose breath test will be agreed on

- One to three days before the lactulose or sham test the volunteer collects a fecal and a urine sample using the restrooms of his/her workplace at the Institute of Microbiology, ETH Zurich and directly snap-freeze it using liquid nitrogen. The samples will be stored by the proband at -80°C (at biosafety level 2).

- a lactulose breath test or a sham test will be carried out

- Within the next two days, the proband will collect a fecal and urine sample at his/her workplace, snap-freeze it and store it at -80°C.

- 14 days after the lactulose breath test, the volunteer will take additional fecal and urine samples following the same procedure.

- Finally, all stool and urine samples will be assembled at ETH for further processing.

- 1. List of abbreviations

AE Adverse Event

BMI Body Mass Index

CRF Case Report Form

GCP Good Clinical Practice

GI Gastrointestinal

LHT Law on human research

HMG Heilmittelgesetz

ICH International Conference on Harmonisation

IEC Independent Ethics Committee

ClinO Clinical Trial Ordinance

i.g. Intragastric

h hour

g gramm

Art.nr article number

BL2 Biosafety Level 2

1. INTRODUCTION
   1. Background

Humans and other animals coexist with trillions of microbes on their body surfaces, collectively referred to as microbiota. One of the key benefits these microbes confer to their host is colonization resistance (CR), i.e. protection against invasion and infection by pathogens. It is conceivable that during gut colonization, the pathogen has to compete with the resident intestinal microbiota for nutrients and binding sites (nutrient-niche hypothesis) [1, 2]. Yet, the mechanistic details underlying the protective effect by the microbiota have to be elucidated.

During murine infections with *Salmonella* Typhimurium (*S*. Tm), colonization resistance can be disrupted by disturbing the microbiota via antibiotic treatment [2-4]. Likewise, according to the nutrient-niche hypothesis, providing the ecosystem with an additional nutrient should also open new niches, which might reduce colonization resistance for certain pathogens. To test this hypothesis, we fed mice with the disaccharide lactulose, which cannot be absorbed during the passage through the host's small intestine [5, 6]. Therefore, it enriches the nutrient pool available to the gut microbes in the large intestine. *S*. Tm cannot grow on lactulose itself but might profit directly or indirectly from the sugar monomers galactose and fructose which are released upon degradation of lactulose by certain members of the gut microbiota [7, 8]. Lactulose-feeding of CR-proficient mice resulted in a significantly higher colonization and inflammatory responses by *S*. Tm than in untreated mice. Therefore, the increased intake of lactulose seems to rise the infection risk for this enteropathogen.

These findings have direct medical implications, as lactulose is used as a food ingredient (named galactofructose), for the treatment of constipation and hepatic encephalopathy, and in the lactulose breath test to diagnose small intestinal bacterial overgrowth [9].

- 1. Rationale for current study

In this study, we aim at monitoring the effects of lactulose intake on human patients undergoing a lactulose breath test. In particular, we would like to monitor shifts in the microbial metabolic landscape and microbial composition (e. g. enterobacterial blooms) as a direct consequence of lactulose uptake.

- 1. Aim and significance of the project

The results gained from these analyses will help us to elucidate the nutritional effects of non-digestible polysaccharides on the microbiota composition and its metabolites. Furthermore, the insights might challenge the concept of prebiotics, as they might not be exclusively beneficial but also be unsafe by opening new niches for pathogenic invaders.

- 1. Categorization of the study

This study is classified as risk category A, as it is a health-related study intervention with only minimal risk and burdens and as the lactulose breath test is performed routinely as a diagnostic method.

1. STUDY DESIGN

This is a clinical study in healthy volunteers aiming to investigate the influence on lactulose intake on the gut microbiota composition and on microbiota-dependent metabolites.

- 1. Primary and Secondary objectives

**Primary objective:**

- Change in microbial community composition upon lactulose intake

**Secondary objectives:**

- Changes in metabolic profiles upon lactulose intake within the gut microbial community (measured in fecal samples) and its impact for the host metabolism (measured in urine samples).
- Inflluence of basic epidemiological parameters (age, gender, country of origin, exercise, smoking) on composition of gut microbiota.
- Influence of microbiota on hydrogen concentration in lactulose breath test
  1. Study procedures, methods outcomes

For this study we will recruit healthy volunteers from ETH Zurich/University of Zurich. Only individuals with training and experience handling liquid nitrogen and -80°C freezers (BL2) will be included in this study. The volunteers will use goggles, gloves and will wear lab coats to snap-freeze the fecal samples. For encoding, cryo-tubes will be labeled with the study number and the day only and the name and personal information will only be known to the physician recruiting the proband for the study. .

The first sample of stool and urine will be collected by the proband one to three days before the lactulose breath test (date will be indicated on the tube). Subsequently, the volunteers will undergo a lactulose breath test or a sham test. Probands will be randomized using a sealed envelope method to receive either 50g lactulose or 50g sucrose in 200 ml water. The study design will be double blinded and neither the study nurse nor the proband will know about group assignment. After ingestion of lactulose/sucrose, hydrogen concentrations in the breath of the individuals will be monitored (baseline level, 30 min, 60 min and 120 min after lactulose/sucrose intake).

Within the next two days, the proband will collect a fecal and urine samples during his or her working hours as described above (date will be indicated on the tube). 14 days after the breath test, a third fecal and a third urine sample will be collected.

Before the study, there will be one study visit to inform the probands and to obtain informed consent and address basic medical history and gastrointestinal complaints. This is done by one of the MDs in a seminar room at the Institute of Microbiology, ETH Zürich. Specifically, probands will be asked about loss of appetite, nausea, early satiety, sense of abdominal fullness, vomiting, abdominal pain, dysphagia, heartburn, reflux, sweating/ shivering after meals and diarrhea. In addition, probands will be asked about their current medication (proton pump inhibitors, antibiotic therapy, laxative drugs within the last four weeks) previous abdominal surgery, additional chronic diseases, pregnancy, and current or past (≤2 weeks) participation in addition clinical trials (questionnaire Appendix), eating habits (vegetarian, vegan), ethnicity, smokers/non-smokers, the amount of regular physical exercise, stool frequency/consistency (Bristol Stool Scale), weight and height.

The study will be finished within approximately 16 days for each individual. The study includes one examination of approximately 4 hours, the remaining parts of the studies (collection of feces and urine and proper storage of these samples) will be done at the working place of the proband (ETH Hoenggerberg, Zurich).

The anticipated study duration for is from October 2014 to March 2016. Total study duration for each participant is 4 hours maximum (including preparation time) at the study center for the breath test plus collection of fecal samples and urine.

- 1. Method of Randomization and Blinding

To randomly assign our probands to lactulose/sucrose groups, we will apply a sealed envelope technique. Lactulose and sucrose (supermarket) will be filled in tubes labeled with numbers indicated within the envelope. That way, neither the proband nor the study nurse/PI will know the group assignment. Randomization will be ensured using the following program:

<http://www.graphpad.com/quickcalcs/randomize1.cfm>

- 1. Method of encryption

To ensure encryption of samples , cryotubes with fecal and urine samples will be pre-labeled with the study number and the respective date respectively to the breath test. The key for encryption will be stored at University Hospital Zurich. Therefore, only the principal medical investigator, but not the microbiologists will be able to decode the study number and assign this identifier to an individual.

- 1. Unblinding Procedures (Code break)

An Emergency Code Break will be available to the investigator. This Code Break should be opened only in emergency situations when the identity of the investigational intervention must be known by the investigator in order to provide appropriate medical treatment.

1. Recruitment / Participant Entry / Discontinuation
   1. Pre Registration Evaluations

Volunteers will be recruited via public advertisement on notice boards at ETH Hoenggerberg Zurich, as well as by an Email to all members of the Institute of Microbiology and other departments at ETH Hoenggerberg. Exemplary advertisements/Email for potential volunteers are shown in the appendices. Potential volunteers can contact [name], who will give a short summary of the aim and benefits of the study and will check whether the potential volunteers can be included in the study (inclusion criteria/exclusion criteria). No individual-related data will be registered during this telephone interview. (See document 4b-Rekrutierung_Telefonfragebogen).

Interested subject will receive study information by email. Medical history and current treatment will be extracted through a standardized interview before the study after informed consent has been obtained. This is done by one of the MDs in a seminar room at the Institute of Microbiology, ETH Zürich.

- 1. Inclusion criteria

• Subjects free of abdominal complaints or symptoms

• Written informed consent

• Working at ETH Zurich/University of Zurich and trained and experienced in handling liquid nitrogen/-80°C freezers at biosafety level 2.

• Age: 18 to 85 years

- 1. Exclusion criteria
- Previous history of gastrointestinal disease or surgery (excludes appendectomy, hernia repair and anorectal disorders)
- Known diabetes mellitus, scleroderma, neurological impairment or other major current disease
- Subjects with antibiotic therapy, proton pump inhibitors or laxatives within the last four weeks.
- Pregnancy beyond week 12. The lactulose breath test is safe also during pregnancy; however, pregnancy might alter the human microbiota and there is a slight risk that advanced pregnancy would be a confounder in our study. No pregnancy test will be performed.
- Involvement in any other clinical trial as proband during the course of this trial or within a period of 14 days prior to its beginning
  1. Criteria for discontinuation

Subjects may be discontinued from study treatment and assessments at any time, at the discretion of the Principle Investigators. Specific reasons for discontinuing a subject from this study are:

• Withdrawal of informed consent

• Protocol non-compliance (protocol deviation)

- - 1. Voluntary discontinuation by a subject

Subjects are free to discontinue their participation in the study at any time. Subjects who discontinue from the study should always be asked about the reason(s) for their discontinuation and about the presence of any adverse events. Adverse events should be followed up. Data of these probands will be analyzed. However, data of probands will be anonymized and all contact data and identifying information will be deleted from the subject identification log..

1. Efficacy variables

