**Metabolite composition:**

- Monitoring compositional metabolic changes requires the identification and quantification of large portions of metabolites that constitutes these metabolomes. Such global profiling of samples can be achieved by untargeted metabolomics on the basis of mass spectrometry [21]. After metabolite extraction ([name] lab), samples will be analysed by the [name] lab, Institute of Molecular Systems Biology, ETH Zurich. Additional metabolic analyses are also possible.
  1. Lactulose breath test

The lactulose breath test will be evaluated according the standard procedures using established algorithms. Hydrogen concentrations on both groups (lactulose vs. sucrose intake) will be compared using the Mann-Whitney U test.

- 1. Significance level

Significance levels will be determined as described in [12].

- 1. Dropouts

Dropouts will be replaced until 40 (20 for each group) complete sets of samples including the results for the lactulose breath test are available.

1. Study related regulatory issues
   1. Recruitment and Informed Consent

Prior to study enrolment, written informed consent must be obtained from each subject. It is the responsibility of the investigator to obtain this written informed consent after adequate explanation to the subject of the aims, methods, source of funding, the anticipated benefits and potential risks of the study and the discomfort it may entail. Written informed consent should be obtained prior to screening, with the understanding that consent may be withdrawn at any time without prejudice. Two copies of the informed consent are signed: one is given to the subject and one is retained in the Investigator Site File on site.

The right of the participant to refuse to participate without giving reasons must be respected. All participants are free to withdraw at any time from the protocol without giving reasons and without prejudicing possible future treatments at our facility. There is no state of dependence between the proband and the investigators.

- 1. Confidentiality

The Principal Investigator will preserve the confidentiality of participants taking part in the study and is registered under the Data Protection Act.

- 1. Funding

Prof. [name], Institute of Microbiology, ETH Zurich and "Klinik für Gastroenterologie and Hepatologie", Universitätspital Zürich, are funding this study.

- 1. Participant compensation

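### The breath-hydrogen schedule (0, 30, 60 and 120 min) leaves one reading or none after colonic arrival if lactulose takes more than 60 min to get there, which weakens the secondary hydrogen objective

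*Protocol*

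**What the plan says.** Section 4.2 of the protocol (Study procedures) sets the breath readings at "baseline level, 30 min, 60 min and 120 min after lactulose/sucrose intake". Nothing is read between 60 and 120 min, and nothing after 120 min.

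The secondary objectives in section 4.1 include "Influence of microbiota on hydrogen concentration in lactulose breath test". The microbiota is sampled in stool. The Background (section 3.1) says that lactulose is not absorbed in the small intestine and that "it enriches the nutrient pool available to the gut microbes in the large intestine".

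On time available, section 4.2 says "The study includes one examination of approximately 4 hours". The synopsis and section 4.2 also give 4 hours as a maximum that includes preparation.

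On evaluation, section 8.2 refers to standard procedures and established algorithms without naming them, and says that hydrogen in the two arms "will be compared using the Mann-Whitney U test". Section 8.4 sets the group size: "Dropouts will be replaced until 40 (20 for each group) complete sets of samples", with breath-test results included in a complete set.

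**The concern.** The hydrogen that bears on this objective is produced once the dose reaches the large intestine. How much of it the schedule can see therefore depends on when the dose arrives. If arrival is late, the response rests on a single reading at an unknown point of the rise, or is not recorded at all. A participant whose microbiota makes much hydrogen but whose transit is slow would then look like one whose microbiota makes little.

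At stake is the interpretation of the association between microbiota and hydrogen, and to a lesser degree the contrast between lactulose and sucrose. The sampling times belong to the protocol: no later choice of summary measure or test can recover readings that were never taken.

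**Working it through.** The protocol states no effect size, variability or power for hydrogen, so there is no figure of its own to reproduce. The check has two steps.

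**Step 1: readings left after arrival (no outside figure needed).** The post-dose readings are at 30, 60 and 120 min (section 4.2). For a dose arriving in the large intestine at time T:

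- T before 30 min: 3 readings follow
- T from 30 to under 60 min: 2 readings follow
- T from 60 to under 120 min: 1 reading follows (120 min)
- T at 120 min or later: 0 readings follow

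With one reading, neither the peak nor the time of the rise can be determined. The onset can be placed only within a 60-minute interval.

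**Step 2: how many participants this could affect (assumption).** The protocol gives no transit time. I assume T is lognormal with median m and log-SD s = 0.35, and take 20 lactulose recipients (section 8.4). With Φ the standard normal distribution function:

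- two or more readings: Φ(ln(60/m)/s)
- one reading: Φ(ln(120/m)/s) − Φ(ln(60/m)/s)
- none: 1 − Φ(ln(120/m)/s)

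Worked example, m = 90: ln(60/90)/0.35 = −1.158, so Φ = 0.123. ln(120/90)/0.35 = 0.822, so Φ = 0.794. One reading: 0.794 − 0.123 = 0.671. None: 1 − 0.794 = 0.206.

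| Assumed median (min) | Two or more readings | One reading | None | None, of 20 |
|---|---|---|---|---|
| 45 | 79% | 20% | 0.3% | about 0 |
| 60 | 50% | 48% | 2% | about 0.5 |
| 75 | 26% | 65% | 9% | about 2 |
| 90 | 12% | 67% | 21% | about 4 |
| 105 | 5% | 59% | 35% | about 7 |
| 120 | 2% | 48% | 50% | 10 |

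**Sensitivity to the distribution.** A normal model with mean 90 and SD 30 min gives 16% with two or more readings, 68% with one and 16% with none: about 14 and 3 of 20 for the last two. With mean 45 and SD 30 the shares are 69%, 30% and 1%. The pattern does not depend on the lognormal shape.

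**Effect of a later last reading.** Replacing 120 by 180 in the last formula, the share with no reading after arrival becomes 0.6%, 2%, 6% and 12% for medians of 75, 90, 105 and 120 min. For medians of 45 and 60 min it is below 0.1%.

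**Is the arm comparison still usable?** Take the worst row, where 10 of 20 lactulose recipients have not responded by 120 min. Assume that these 10 look like sucrose recipients and that the other 10 exceed every sucrose value. Then P(lactulose value > sucrose value) = 0.5 × 1 + 0.5 × 0.5 = 0.75, so U = 0.75 × 400 = 300 against 200 expected. The SD of U is √(20 × 20 × 41/12) = 37.0, and z = 100/37.0 = 2.7 (p about 0.007). At 21% not responding, P = 0.79 + 0.21 × 0.5 = 0.895, U = 358 and z = 4.3. The comparison is diluted but, on that favourable assumption about the responders, not lost.

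**The case against.** The strongest reply is that the consequence depends on a transit time that the protocol does not contain. If most doses arrive before 60 min, two or three readings follow and the schedule does its job: at a median of 45 min, 79% have two or more readings and almost nobody has none. This stands, and it is why the point is conditional and the range starts near zero. A reader might infer that the colonic response is certain to be missed or to rest on one reading. The documents do not support that.

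A reader might also infer that the association must be biased toward none. That is not established. If transit is unrelated to the microbiota, late arrival adds noise and attenuates the association. If the two are related, transit is a confounder and the direction is uncertain. Stool frequency and Bristol consistency are recorded at the first visit and could serve as rough proxies for transit, but they do not time the arrival of this dose.

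Third, the objective can be read as hydrogen as the routine test reads it. Section 8.2 says "The lactulose breath test will be evaluated according the standard procedures using established algorithms", and the reference list includes a source on hydrogen breath tests that is not available here. Whether the four time points follow a recognised standard cannot be judged from the documents. That limits the point but does not remove it, because the objective concerns the influence of the microbiota and the background places the action of lactulose in the large intestine.

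Finally, the choice of summary measure for hydrogen can properly wait for the SAP, so its absence is not part of this point. Nor is the 4-hour visit a contradiction with two hours of readings: it includes preparation, and shows only that there may be room.

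**Conclusion.** The point holds in conditional form. It follows from the schedule alone that arrival after 60 min leaves one reading and arrival after 120 min leaves none, so that a low value cannot then be separated from slow transit. How often this happens is an assumption: with log-SD 0.35 and medians from 45 to 120 min, between 0.3% and 50% of lactulose recipients have no reading after arrival, and between 20% and 67% have only one. From a median of 60 min upwards, at least half have at most one.

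The consequence is noise in the microbiota–hydrogen association, or confounding by transit of uncertain direction, and some dilution of the arm comparison, which remains feasible. The primary objective on microbial composition does not use these readings and is unaffected. This is a worthwhile, inexpensive improvement to one secondary objective, not a threat to the trial.

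**What to change.** In section 4.2, add breath readings between 60 and 120 min and after 120 min, for example at 90, 150 and 180 min, in both arms and with the same device, as far as the 4-hour maximum including preparation allows. State the transit time that the window is meant to cover.

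If the visit cannot hold the extra readings, reword the objective in section 4.1 so that it concerns hydrogen up to 120 min, and acknowledge that low values may reflect slow transit.

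The cost is a few more non-invasive breaths per participant and possibly a longer stay within the planned visit. No extra visit or equipment is needed, and if transit proves fast the added readings do no harm.
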